**Methods:**

This single-center, open-label, randomized controlled trial will enroll 201 adult parturients undergoing lower segment transverse cesarean section. Participants will be randomized in a 1:1:1 ratio into three groups (*n* = 67 each): Group LB will receive bilateral quadratus lumborum block with liposomal bupivacaine under ultrasound guidance. Group R-P will receive bilateral quadratus lumborum block with ropivacaine in combination with patient-controlled intravenous analgesia. Group P will receive standard patient-controlled intravenous analgesia without regional nerve block. The primary outcome is postoperative pain intensity, assessed using the Visual Analogue Scale during standardized movement at 12, 24, 48, and 72 h postoperatively. A generalized estimating equation model will be used to assess the overall effect of treatment group on pain scores over time. Secondary outcomes include patient-reported Quality of Recovery-15 scores at 24 and 48 h postoperatively; Visual Analogue Scale for pain at rest, measured at 12, 24, 48, and 72 h postoperatively; need for rescue analgesia; postoperative anxiety (assessed by Visual Analogue Scale at 72 h); subjective sleep quality; maximum walking duration; patient satisfaction with analgesia; incidence of nausea and vomiting; postoperative sufentanil consumption and length of hospital stay. Safety outcomes include allergic reactions, wound infection, lightheadedness, headache, circumoral numbness, tongue paresthesia, drowsiness, irritability, blood pressure fluctuations (hypotension, hypertension), respiratory depression (hypoventilation), and cardiac events (bradycardia, tachycardia, arrhythmia, cardiac arrest). Data will be analyzed using a modified intention-to-treat approach.

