### Secondary outcomes

2.5

Secondary outcomes will include patient self-assessment of the Quality of Recovery-15 (QoR-15) scale at 24 and 48 h postoperatively, as well as Visual Analog Scale (VAS) pain scores at rest, recorded at 12, 24, 48, and 72 h post-surgery. Additionally, the number of postoperative acute analgesic requests will be documented. Postoperative anxiety regarding the hypothetical repeat cesarean section will be assessed at 72 h post-surgery using the VAS score (scores range from 0 to 10, with 0 indicating the best and 10 indicating the worst, named VAS anxiety score) (19). Subjective sleep quality will be evaluated for 24, 48, and 72 h post-surgery using the Numerical Rating Scale (NRS) (scores range from 0 to 10, with 0 indicating the worst and 10 indicating the best sleep quality). The maximum walking duration, defined as the longest duration a patient can walk after surgery, will be measured at 24, 48, and 72 h post-surgery. Patient satisfaction with analgesic management will be assessed at 24, 48, and 72 h post-surgery using the NRS (scores range from 0 to 10, with 0 indicating the worst and 10 indicating the best). Postoperative opioid use (including sufentanil via PCIA and any rescue oxycodone) will be recorded over the 0–72 h period. For comparability, all opioid doses will be converted to intravenous morphine milligram equivalents (MME) using standard equianalgesic conversion factors. Both the raw consumption of sufentanil and oxycodone as well as the total MME will be reported. Furthermore, the incidence of nausea and vomiting and length of hospital stay will be recorded.

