### Anaesthetic and study interventions

2.8

All patients fast for at least 8 h and abstain from water for 4 h preoperatively. In the operating room, after establishing a peripheral intravenous channel, they inhale oxygen at 5 L/min via mask, with continuous monitoring of vital signs: non-invasive blood pressure, percutaneous arterial oxygen saturation (SpO_2_), heart rate, and respiratory rate. Preoperatively, all parturients will receive combined spinal-epidural anesthesia. The parturient will be placed in the lateral decubitus position. Following standard aseptic skin preparation and draping with a sterile aperture sheet, subarachnoid blockade will be performed. At the L2/3 or L3/4 interspace, 10–14 mg of 0.5% ropivacaine will be administered intrathecally to achieve rapid onset of surgical anesthesia. An epidural catheter will then be inserted for subsequent intraoperative supplementation if required. In case of inadequate block height or duration, incremental boluses of 2% lidocaine (3-5 mL) or 1% ropivacaine (5 mL) will be administered through the epidural catheter, with careful titration based on the patient’s response and hemodynamic status. Continuous monitoring will be maintained for signs of local anesthetic systemic toxicity, such as tinnitus, perioral numbness, or altered mental status. For parturients with extreme body habitus or height (affecting drug distribution and blockade levels), local anesthetic dosing will be precisely calibrated based on individual anthropometric measurements to optimize analgesic efficacy and safety. Dosing will be precisely calibrated in accordance with each patient’s anthropomorphic measurements to ensure optimal analgesic outcomes. Upon verification of both the requisite analgesic level (at least T6) and the efficacy of the blockade, the cesarean section will be initiated. Supine hypotensive syndrome and total spinal anesthesia are medical emergencies requiring immediate treatment, so, intensive monitoring during the surgical procedure and maintaining hemodynamic stability with the utilization of vasoactive medications as needed to support vital sign parameters are essential. All patients will receive postoperative analgesic regimens as dictated by the sealed-envelope protocol. This information is exclusively known to the anesthesiologist administering the anesthesia, with all other individuals involved remaining blinded to the details. Participants in group LB will receive bilateral QL nerve block [posterior QL block (20)] utilizing liposomal bupivacaine injection under ultrasound guidance (Liposomal bupivacaine injection, 133 mg per 20 mL on each side); participants enrolled in group R-P will receive bilateral QL nerve block utilizing ropivacaine injection under ultrasound guidance (Ropivacaine injection, 20 mL of 0.375% ropivacaine on each side), in conjunction with a PCIA; and participants enrolled in group P will be managed with standard PCIA, without supplementary nerve block interventions. In the preparation of PCIA pumps, each total volume is standardized at 100 mL, and the formulation includes sufentanil and 8 mg of ondansetron. The total amount of sufentanil is calculated based on a dosage of 2 μg per kilogram of body weight. The background infusion rate is set within the range of 0.04 μg/kg/h. The PCIA protocol is set with a 0.04 μg/kg bolus dose and a 15-min lockout interval to ensure safety.

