### Data collection and monitoring

2.9

Data collection will encompass a range of patient characteristics, including age, height, weight, body mass index (BMI), ASA score, drinking status, smoking status, parity, duration of surgery, intraoperative bleeding, and intraoperative analgesia grade. All pertinent data will be meticulously recorded in case report forms (CRFs) and subsequently inputted into an electronic database under the vigilant supervision of the principal investigator (Table 1). An independent Data Monitoring Committee (DMC) will be tasked with the ongoing oversight of the data collection process. Upon completion of data registration, the electronic database will be safeguarded. De-identified datasets will then be forwarded to an independent statistician for comprehensive analysis in accordance with a predefined statistical plan. Any serious adverse events (SAEs), whether or not they are related to the study medication (e.g., persistent hemodynamic instability), must be promptly reported to the principal investigator. In such instances, the perioperative care team is obligated to implement necessary measures to safeguard participant wellbeing. Furthermore, these SAEs must be communicated to the DMC within a 24-h window for thorough discussion and to determine if any adjustments to the study interventions or the study’s discontinuation are warranted.

**Table 1 tab1:** Schedule of patient enrolment, study interventions and outcome assessment.

	Study period							
	Enrollment	Allocation	Post-allocation					Close-out
Time point	Pre-op visit	Pre-op 1 day	0 h post-op	12 h post-op	24 h post-op	48 h post-op	72 h post-op	Discharged
Patient enrolment								
Eligibility criteria	×							
Written informed	×							
Consent								
Demographic data	×							
Baseline characteristics	×							
Randomization/allocation		×						
Study interventions								
Liposomal bupivacaine			×					
Ropivacaine & PCIA			×					
PCIA			×					
Outcome assessment								
VAS pain score during turning over				×	×	×	×	
VAS pain score at rest				×	×	×	×	
QoR-15 scale					×	×		
Need for rescue analgesia				×	×	×	×	
VAS anxiety score							×	
NRS sleep score					×	×	×	
Maximum walking duration					×	×	×	
NRS for satisfaction with analgesic					×	×	×	
Opioid consumption								×
Length of hospital stay								×
Nausea			×	×	×	×	×	
Vomiting			×	×	×	×	×	
Adverse events								
Allergy			×	×	×	×	×	
Wound infection			×	×	×	×	×	
Lightheadedness			×	×	×	×	×	
Headache			×	×	×	×	×	

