### Statistical analysis

2.11

The normality of continuous variables will be assessed using the Shapiro–Wilk test. Data following a normal distribution will be reported as mean (standard deviation, SD), while non-normally distributed data will be presented as median (interquartile range, IQR). Binomial variables will be expressed as proportions. A generalized estimating equation (GEE) model will be used to analyze repeated measures of continuous variables, including VAS scores, QoR-15 scores, maximum walking duration, and subjective sleep quality, accounting for within-subject correlations. The correlation structure will be selected based on the quasi-likelihood under the independence model criterion (QIC). Data distribution will determine the use of either a normal or gamma distribution with identity or log-link functions. *Post hoc* pairwise comparisons will be Bonferroni-corrected. Continuous variables measured at a single time point, such as hospital stay and sufentanil consumption, will be analyzed using *t*-tests or Mann–Whitney U tests depending on normality. Categorical data will be analyzed using the *χ*^2^ test, with *p*-values adjusted using the Bonferroni method and set at 0.017 for pairwise comparisons. Statistical significance will be defined as *p* < 0.05.

All study outcomes will be analysed in the modified intentiontotreat population, including all patients who undergo randomisation with relevant data available. Patients will be included in the analysis according to their original allocation. Multiple testing corrections for secondary outcomes will not be applied; therefore, these outcomes should be interpreted as exploratory findings. Odds ratios (OR) and corresponding 95% confidence intervals (CI) will be reported where appropriate. No interim analysis will be planned. Missing data will not be imputed. Statistical analyses will be performed using SPSS (version 25.0; IBM SPSS). A two-sided *p*-value < 0.05 will indicate statistical significance, except where false discovery rate (FDR) corrections apply.

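### The opioid variable named for testing is sufentanil alone, which Group LB does not receive by design, so the named comparison cannot answer the opioid-sparing question

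*Protocol article*

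**What the plan says.** The protocol article describes the opioid outcome in several places.

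- **Section 2.5, Secondary outcomes:** "Postoperative opioid use (including sufentanil via PCIA and any rescue oxycodone) will be recorded over the 0–72 h period". All opioid doses are to be put on a common intravenous MME scale, and "Both the raw consumption of sufentanil and oxycodone as well as the total MME will be reported".
- **Abstract, Methods:** the list of secondary outcomes ends with "postoperative sufentanil consumption and length of hospital stay". It mentions no oxycodone, no MME and no time window.
- **Section 2.11, Statistical analysis:** for continuous outcomes with one value per patient, the text reads "such as hospital stay and sufentanil consumption, will be analyzed using". The test is a t-test if the data look normal and a Mann–Whitney U test otherwise. Neither MME nor oxycodone appears in this section.
- **Section 2.9, Table 1:** the row "Opioid consumption" has one mark, in the discharge column. The 72 h cell is blank.
- **Section 3, Discussion:** the outcome is called opioid consumption, without components.

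Section 2.8 sets the regimens. "Participants in group LB will receive bilateral QL nerve block" with liposomal bupivacaine, and no PCIA is listed for that group. Group R-P receives a ropivacaine block plus PCIA, and Group P receives PCIA alone. Sufentanil appears only as a constituent of the PCIA pump. Oral oxycodone is second-line rescue after paracetamol, with no restriction by group.

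**The concern.** Sufentanil alone and sufentanil plus oxycodone are different variables. They can rank the arms differently, and only one of them measures opioid use in all three arms. The variable named in section 2.11 counts a drug that Group LB is not scheduled to receive and leaves out the one postoperative opioid that it may receive.

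Opioid sparing is central to the trial's rationale. The Discussion says that the three-arm design is meant to show whether LB reduces reliance on systemic opioids compared with PCIA alone, and how LB compares with the ropivacaine regimen in opioid-sparing potential. Lower opioid consumption is part of the stated hypothesis, and the Conclusion makes opioid reduction a specific focus. A test result fixed by the treatment assignment could be read as evidence for that claim when it carries none. The trial is open-label, and leaving two definitions in place also leaves a choice of definition open at the analysis stage.

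**Working it through.** The plan gives no figure of its own to reproduce here. The check compares the definitions and then works out what the named test would show.

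**1. Opioids listed after surgery, by arm (sections 2.8 and 2.5)**

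| Arm | Sufentanil (PCIA) | Rescue oxycodone |
|---|---|---|
| LB | not listed, so 0 µg | possible |
| R-P | background infusion plus boluses, so above 0 | possible |
| P | background infusion plus boluses, so above 0 | possible |

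The pump delivers a background infusion (0.04 µg/kg/h), so a patient on the pump has consumption above zero even without pressing for a bolus.

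**2. What the sufentanil test of LB against a pump arm shows**

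Inputs: n₁ = n₂ = 67 (section 2.10), all LB values 0, all pump-arm values above 0 and untied.

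- Every pump-arm value exceeds every LB value, so U = 0.
- Mean of U under the null: 67 × 67 / 2 = 2244.5.
- Variance with a correction for the 67 tied zeros, N = 134: (67 × 67 / 12) × [135 − (67³ − 67) / (134 × 133)] = 374.08 × (135 − 16.87) ≈ 44,190, so SD ≈ 210.2.
- With continuity correction, z = (2244.5 − 0.5) / 210.2 ≈ 10.7, and the two-sided p ≈ 1.3E-26.

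The amounts in the pump arm do not enter this result; it is enough that they are above zero. With 60 analysed per arm instead of 67, p ≈ 5.7E-24. The same holds for LB against P and for LB against R-P. Of the three pairwise contrasts, the two that involve LB are settled by the allocation. Only R-P against P is not.

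**3. How much of the 0–72 h window sufentanil can describe**

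The pump contains 2 µg/kg and the background rate is 0.04 µg/kg/h (section 2.8). On background alone the content lasts 2 / 0.04 = 50 h, and less with boluses. Whether the pump is refilled is not stated. If it is not, oxycodone is the only listed opioid in any arm for at least the last 72 − 50 = 22 h of the window. Sufentanil alone would then be an incomplete measure in the pump arms as well.

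**4. Time window**

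Section 2.5 fixes 0–72 h. The abstract and section 2.11 give no window, and Table 1 gives a collection point (discharge), not an accumulation period.

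**The case against.** The best defence is that section 2.11 does not limit testing to sufentanil. The words *such as* introduce examples. Total 0–72 h MME is one continuous value per patient, so the same sentence covers it and assigns it the same test. The abstract's wording can be taken as a short label for the full definition in section 2.5. This stands in part: a test of MME is not ruled out. But the only opioid variable that the analysis section names is the one that cannot inform the LB contrasts, and the abstract repeats it.

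A reader might go further and infer that the plan conceals rescue opioid use in Group LB. The documents do not support that. Section 2.5 commits to reporting raw oxycodone and total MME, and the need for rescue analgesia is recorded at 12, 24, 48 and 72 h in Table 1. The problem concerns which variable is named for testing; what is reported is not in doubt.

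A reader might also infer from Table 1 that the total runs to discharge and so mixes opioid need with length of stay. That does not follow. A mark at close-out is compatible with reading a 0–72 h total from the records at that point, and no section defines a total up to discharge.

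Nor do the documents allow a forecast of how much oxycodone LB patients will take. Dosing at every permitted 4–6 h interval for 72 h would be 12 to 18 doses (72/6 and 72/4). That is an extreme, because oxycodone is given only after paracetamol has proved insufficient or its daily maximum has been reached.

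Finally, the endpoint is secondary, and section 2.11 calls secondary outcomes exploratory. That is correct and limits the weight of the point.

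**Conclusion.** The point holds as an inconsistency in the named opioid variable. Sufentanil alone (abstract, section 2.11) does not match sufentanil plus oxycodone in MME over 0–72 h (section 2.5). Tested as named, the comparison of LB with P or R-P would be significant at about p = 1E-26 whatever the analgesic effect, and so says nothing about opioid sparing.

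This rests on two assumptions taken from the listed regimens: LB patients receive no PCIA sufentanil, and every analysed pump patient receives some. A few departures from allocation would make the p-value less extreme without making the test informative.

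The Table 1 timing is a minor alignment matter. The primary outcome, its analysis and the sample size are not affected.

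**What to change.** - In section 2.11 and the abstract, name total 0–72 h opioid consumption in intravenous MME (sufentanil plus oxycodone) as the opioid variable compared between arms.
- Report sufentanil and oxycodone separately by arm as descriptive components, with no test of sufentanil that involves Group LB.
- Add a note to Table 1 that the total recorded at discharge covers 0–72 h.

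The cost is wording in two places and one table note. Section 2.5 already commits to collecting every component and to the conversion, so no new data are needed. The downside is that the opioid-sparing estimate may look less favourable to LB than a sufentanil comparison would. One limit remains: total MME in the pump arms still includes the protocol-set background infusion, so part of the difference from LB continues to reflect the regimen. Reporting the components beside the total lets readers see how much.

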### Safety outcomes

2.6

Safety outcomes will assess postoperative adverse reactions including, allergy, wound infection, lightheadedness, headache, circumoral numbness, tongue paresthesia, drowsiness, irritability, hypotension, hypertension, hypoventilation, bradycardia, tachycardia, arrhythmia, and cardiac arrest.

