### Sample size calculation

2.10

Based on previous studies (21–23), a minimum change of at least 1.40 in the VAS pain score is considered to be clinically significant, denoting a substantial alteration in pain perception. The standard deviation (SD) of 1.55, derived from these studies, quantifies the variability in pain measurements. Using a two-sided significance level (*α*) of 0.05 and a desired statistical power of 80%, the initial sample size calculation based on a *t*-test indicated that a minimum of 20 participants per group would be necessary to detect a clinically significant change. This calculation assumed a single measurement per patient. However, the primary analysis includes 4 repeated measurements per patient, which increases the statistical power. To account for the correlation among repeated measures, we incorporated an intraclass correlation coefficient (ICC) of 0.53 into the sample size calculation. Additionally, to address multiple pairwise comparisons among the three study groups, we applied the Bonferroni correction, adjusting the significance level from 0.05 to 0.017 (0.05/3). The final sample size was calculated using the following formula for repeated measures: The formula is 
$n=\frac{{\left(Z1-\alpha /2+Z1-\beta \right)}^{2}\times (1+(\kappa -1)\rho )\times \sigma^{2}}{\Delta^{2}\times (1-\rho )}$
 (*n* is the sample size required per group, 
κ
 is the number of repeated measurements (4 in this study), 
σ
 is the standard deviation (1.55), 
Δ
 is the minimal clinically important difference (1.40), and 
ρ
 is the intraclass correlation coefficient (0.53). After adjusting for repeated measures, Bonferroni correction, and an anticipated dropout rate of 10%, we determined that a sample size of 67 participants per group would be required. Therefore, we plan to enroll a total of 201 patients (67 per group).

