## Discussion

3

In this prospective, randomized, open-label, controlled clinical trial, we will recruit 201 adult parturients undergoing cesarean delivery to assess the efficacy and safety of bilateral QL block with liposomal bupivacaine for post-cesarean analgesia. This study will be implemented in accordance with the Consolidated Standards of Reporting Trials guidelines and address three critical clinical questions regarding the proposed postoperative analgesic strategy. First, whether it fulfills fundamental analgesic requirements. Second, whether it independently achieves contemporary standards for comprehensive pain management. And, whether it confers clinically significant co-benefits beyond analgesia. The primary outcome is postoperative pain intensity, evaluated using the VAS pain score during standardized movement at 12, 24, 48, and 72 h post-surgery. Secondary outcomes include quality of recovery (QoR-15 scores), VAS scores at rest, need for rescue analgesia, postoperative anxiety regarding a hypothetical repeat cesarean section, subjective sleep quality, maximum walking duration, patient satisfaction with analgesia, postoperative nausea and vomiting, opioid consumption, and hospital length of stay.

The three-arm design of this trial was structured to address two key clinical questions regarding post-cesarean analgesia. First, by comparing bilateral QL block with liposomal bupivacaine to standard intravenous analgesia alone, the study aims to evaluate whether a single-injection, long-acting regional technique can provide superior pain control and reduce reliance on systemic opioids. Second, the inclusion of a group receiving QL block with ropivacaine combined with intravenous analgesia allows for a direct comparison between liposomal and conventional local anesthetics in terms of both analgesic efficacy and opioid-sparing potential. This design facilitates a comprehensive assessment of the relative benefits of QL block strategies, not only in improving postoperative pain outcomes but also in minimizing opioid-related adverse effects.

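### Section 2.11 groups safety outcomes by allocation whether or not the study drug was given; if treatments deviate, adverse reactions can be credited to the wrong regimen

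*Protocol article*

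**What the plan says.** Section 2.11 (Statistical analysis) states the population: "All study outcomes will be analysed in the modified intentiontotreat population, including all patients who undergo randomisation with relevant data available". It then states the grouping: "Patients will be included in the analysis according to their original allocation". Entry requires randomisation and data; it does not require that any study drug was given.

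Section 2.6 classes adverse reactions as outcomes: "Safety outcomes will assess postoperative adverse reactions including, allergy, wound infection, lightheadedness, headache, circumoral numbness, tongue paresthesia". The list continues with drowsiness, hypoventilation, arrhythmia and cardiac arrest, among others. It therefore mixes signs of local anaesthetic toxicity with effects that an opioid could produce.

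Safety is a declared aim. The Discussion says that the trial is "to assess the efficacy and safety of bilateral QL block with liposomal bupivacaine for post-cesarean analgesia", and the Conclusion also couples efficacy with safety.

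In Table 1 (section 2.9), the row "Randomization/allocation" is marked one day before surgery, and the three interventions are marked at 0 h after surgery. No safety set, treatment-received grouping or exception for adverse events appears anywhere in the article.

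**The concern.** Adverse reactions follow from what a patient was given, whereas the rule sorts them by what the patient was assigned. A patient allocated to LB who is never injected but is followed for 72 h adds to the LB denominator without having been exposed. If that patient is managed with PCIA and becomes drowsy, the event is tabulated under LB. A patient in another arm who is given liposomal bupivacaine carries any reaction to it into that other arm.

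This is a stated rule, not a detail left to a fuller document: a later plan with a safety set by treatment received would contradict the article. At stake is how accurate the safety table is, in a trial that intends to draw conclusions on safety with 67 patients per arm. At that size, one event is 1/67 = 1.5 percentage points.

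**Working it through.** **Inputs from the documents.** Allocation is 1:1:1 ("Participants will be randomized in a 1:1:1 ratio into three groups") and there are 67 per group (section 2.10, "a sample size of 67 participants per group would be required"). The plan states no figure on this point, so there is none to reproduce. I take 67 as the denominator only; how it was derived does not matter here.

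**Assumed inputs.** The documents give neither a deviation rate nor adverse event rates. I let c, the number of LB-allocated patients not injected, run from 0 to 7. Let pL be the risk of a toxicity event with liposomal bupivacaine and pC the risk without it. The arithmetic is for the contrast of LB with P. Against R-P the size would differ, because R-P also receives a local anaesthetic.

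**One-way deviation.** The expected LB rate by allocation is [(67 − c)·pL + c·pC]/67. Subtracting pC leaves (1 − c/67)·(pL − pC), so the share of the true risk difference that remains is 1 − c/67, whatever the event rates.

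**Two-way deviation.** If c patients cross in each direction, the P rate also rises by (c/67)·(pL − pC), and the share that remains is 1 − 2c/67.

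| c | one-way | two-way |
|---|---|---|
| 0 | 100% | 100% |
| 1 | 98.5% | 97.0% |
| 3 | 95.5% | 91.0% |
| 5 | 92.5% | 85.1% |
| 7 | 89.6% | 79.1% |

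Each uninjected LB patient thus costs 1/67 = 1.5% of the true difference, and each pair crossing over costs 2/67 = 3.0%.

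**In events.** With assumed risks of 10% and 2% and c = 7, the LB rate by allocation is (60 × 0.10 + 7 × 0.02)/67 = 6.14/67 = 9.2%, against 10%. That is 6.14 expected events instead of 6.7, a shift of 0.8 percentage points.

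**In power.** Assume risks of 20% and 5%, two-sided alpha 0.05, and that uninjected patients join P when grouped by drug received. Power is Φ[(d − 1.96·SE0)/SE1], with SE0 pooled and SE1 unpooled. With c = 0, d = 0.15, SE0 = √(2 × 0.125 × 0.875/67) = 0.0571 and SE1 = √[(0.16 + 0.0475)/67] = 0.0557, which gives 75.3%. The same formula gives, by allocation versus by drug received, 72.3% versus 75.7% at c = 3 and 68.0% versus 75.9% at c = 7.

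**Opioid-type events.** These go the other way. One opioid event in an uninjected LB-allocated patient on PCIA adds 1.5 percentage points to the LB rate for an effect that the block did not cause.

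**The case against.** The strongest reply is that nothing may happen. If every patient gets the allocated treatment, the two groupings are identical. The block is given once around the operation, section 2.8 has the anaesthesiologist follow a sealed envelope, and there is no multi-day adherence to lose. The protocol has no rule that moves an LB patient to PCIA or gives a P patient a block; rescue is paracetamol and then oxycodone (section 2.8). Serious events go to the principal investigator whether or not related to study medication, and to the monitoring committee within 24 h (section 2.9), so they are reviewed outside the group table. All of this stands, and it keeps the point modest. The review of serious events does not cover the non-serious reactions that make up much of section 2.6.

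Three stronger readings are tempting, and the documents do not support them.

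- A reader might infer that the rule does dilute the harms of liposomal bupivacaine. It can do so only if deviations occur, and no rate is given.
- A reader might infer that it favours the Discussion's hypothesis of better safety. That hypothesis expects LB to be safer, and drawing the arms together works against showing it. Harm is masked only where LB is truly worse, as it might be for local anaesthetic toxicity; misplaced opioid events count against LB.
- A reader might take the 10% in section 2.10 as the share not injected. It is an allowance for dropout. Dropouts without safety data leave the denominator, since data must be available and nothing is imputed. The upper end of c = 7 used here is an assumption, not an estimate.

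A fair further objection is that grouping by treatment received gives up strict randomisation and is ambiguous for a patient who has a block and later PCIA. A placement rule and a by-allocation supplement are therefore needed.

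**Conclusion.** The point holds in conditional form. Section 2.11 applies analysis by allocation to adverse reactions, in a population that does not require exposure. Where treatment received differs from allocation, that can weaken a local anaesthetic toxicity signal for liposomal bupivacaine and can place opioid-type events under LB. In the contrast with P, the weakening is about 1.5% of the true risk difference per uninjected LB patient and about 3% per pair crossing over. This assumes that an uninjected patient carries the no-drug risk. With few deviations the average shift is below one event; the practical risk lies more in a single rare event tabulated under the wrong regimen. The bias does not run in one direction, and its true size cannot be had from the documents. This is a worthwhile, low-cost correction, not a threat to the primary analysis.

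**What to change.** In section 2.11, limit the by-allocation rule to efficacy outcomes. For the outcomes of section 2.6, make the main analysis a safety set of all randomised patients who received any study block or PCIA, grouped by treatment received.

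Fix the placement in advance:

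- any patient given liposomal bupivacaine counts as LB;
- any patient given a ropivacaine block counts as R-P;
- PCIA without a block counts as P;
- PCIA added after a block, where it was not part of the allocated regimen, is flagged.

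Keep the by-allocation table as a supplement, and list each serious adverse event with both allocation and treatment received.

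The cost is a few lines of text, one extra table and two columns in a listing. Treatment and sample size do not change. The small downside is that the treatment-received groups are not strictly randomised; the supplement covers that.
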